#### Long term follow-up

Permission will be sought from the participant to be contacted annually for follow-up information regarding the participant's health and employment status. The participant will also be invited to remain in contact so that the results may be disseminated to them once published.

### Measures

#### Primary outcome measures – Primary efficacy measures

Since we are interested in changes in both symptoms and disability we have chosen to designate both the symptoms of fatigue and physical function as primary outcomes. This is because it is possible that a specific treatment may relieve symptoms without reducing disability, or vice versa. Both these measures will be self-rated.

The 11 item Chalder Fatigue Questionnaire measures the severity of symptomatic fatigue [27], and has been the most frequently used measure of fatigue in most previous trials of these interventions. We will use the 0,0,1,1 item scores to allow a possible score of between 0 and 11. A positive outcome will be a 50% reduction in fatigue score, *or *a score of 3 or less, this threshold having been previously shown to indicate normal fatigue [27].

The SF-36 physical function sub-scale [29] measures physical function, and has often been used as a primary outcome measure in trials of CBT and GET. We will count a score of 75 (out of a maximum of 100) or more, *or *a 50% increase from baseline in SF-36 sub-scale score as a positive outcome. A score of 70 is about one standard deviation below the mean score (about 85, depending on the study) for the UK adult population [51,52].

Those participants who improve in both primary outcome measures will be regarded as overall improvers.

#### Secondary outcome measures – Secondary efficacy measures

1. The Chalder Fatigue Questionnaire Likert scoring (0,1,2,3) will be used to compare responses to treatment [27].

2. The self-rated Clinical Global Impression (CGI) change score (range 1 – 7) provides a self-rated global measure of change, and has been used in previous trials [45]. As in previous trials, we will consider scores of 1 or 2 as a positive outcome ("very much better" and "much better") and the rest as non-improvement [23].

3. The CGI change scale will also be rated by the treating therapist at the end of session number 14, and by the SSMC doctor at the 52-week review.

4. "Recovery" will be defined by meeting all four of the following criteria: (i) a Chalder Fatigue Questionnaire score of 3 or less [27], (ii) SF-36 physical Function score of 85 or above [47,48], (iii) a CGI score of 1 [45], and (iv) the participant no longer meets Oxford criteria for CFS [2], CDC criteria for CFS [1] or the London criteria for ME [40].

5. The Hospital Anxiety and Depression Scale scores in both anxiety and depression sub-scales [38].

6. The Work and Social Adjustment scale provides a more comprehensive measure of participation in occupational and domestic activities [33].

7. The EuroQOL (EQ-5D) provides a global measure of the quality of life [39].

8. The six-minute walking test will give an objective outcome measure of physical capacity [31].

9. The self-paced step test of fitness [43].

10. The Borg Scale of perceived physical exertion [44], to measure effort with exercise and completed immediately after the step test.

11. The Client Service Receipt Inventory (CSRI), adapted for use in CFS/ME [31], will measure hours of employment/study, wages and benefits received, allowing another more objective measure of function.

12. An operationalised Likert scale of the nine CDC symptoms of CFS [1].

13. The Physical Symptoms (Physical Health Questionnaire 15 items(PHQ15)) [35].

14. A measurement of participant satisfaction with the trial will also be taken at 52 weeks [53].

#### Adverse outcomes

Adverse outcomes (score of 5–7 of the self-rated CGI) will be monitored by examining the CGI at all follow-up assessment interviews [49]. An adverse outcome will be considered to have occurred if the physical function score of the SF-36 [28] has dropped by 20 points from the previous measurement. This deterioration score has been chosen since it represents approximately one standard deviation from the mean baseline scores (between 18 and 27) from previous trials using this measure [23,25]. Furthermore, the RN will enquire regarding specific adverse events at all follow-up assessment interviews.

#### Predictors

1. Sex

2. Age

3. Duration of CFS/ME (months)

4. 1 week of actigraphy [18] (as initiated at visit 1 with the research nurse)

5. Body mass index (measure weight in kg and height in metres)

6. The CDC criteria for CFS [1]

7. The London criteria for myalgic encephalomyelitis [40]

8. Presence or absence of "fibromyalgia" [41]

9. Jenkins sleep scale of subjective sleep problems [37]

10. Symptom interpretation questionnaire [34]

11. Preferred treatment group

12. Self-efficacy for managing chronic disease scale [32]

13. Somatisation (from 15 item physical symptoms PHQ sub-scale) [35]

14. Depressive disorder (major and minor depressive disorder, dysthymia by DSMIV) (from SCID) [30]

15. The Hospital Anxiety and Depression Scale (HADS) [38] combined score

16. Receipt of ill-health benefits or pension

17. In dispute/negotiation of benefits or pension

18. Current and specific membership of a self-help group (specific question)

#### Process variables

1. Step test of fitness [43]

2. Borg Scale of perceived physical exertion [44]

3. The symptom interpretation questionnaire [34]

4. Exercise and activity scale

5. PHQ symptom sub-scale

6. HADS scale combined score

#### Therapeutic input

1. At each RN assessment participants will be asked what other treatments they have been receiving (e.g. complementary and alternative therapies, prescribed and over-the-counter medicines).

2. The strength of the therapeutic alliance will be measured by the therapy integrity rating scale by an independent and blinded observer [53].

3. The differentiation of the supplementary therapies will be measured blind to treatment group by an independent observer [53].

#### Plausibility of therapy

After the first treatment session, all participants will be asked to fill in a brief measure of how plausible their treatment appears to them.

#### Economic costs

The CSRI [42] will retrospectively record service utilisation for the six months prior to the baseline assessment, for the period between baseline and 24 weeks, and then for the period from 24 weeks to 52 weeks. A comprehensive range of services will be included so that in addition to being able to determine the resource implications to the NHS, we will also have information on the impact that treatment has on other parts of the care system as well as on informal carers. The ability to engage in employment, education and work in the home are frequently affected by CFS/ME and the CSRI will collect data on these activities. Service use will be valued by attaching appropriate unit costs from national sources (e.g. Netten et al, 2003 [54]) as well as intervention costs specifically calculated for the study.

#### Adverse Events

Adverse events (AE) are any clinical change, disease or disorder experienced by the participant during their participation in the trial, whether or not considered related to the use of treatments being studied in the trial.

#### Serious Adverse Events (SAEs)

A Serious Adverse Event will be defined according to usual clinical trial definitions and will be reported to the appropriate authorities in the standard manner. If there is any doubt in the minds of the RN and the centre leader as to whether the AE is a serious AE, the centre leader will obtain a second opinion from one of the PIs.

#### Serious Adverse Reactions (SARs)

A Serious Adverse Reaction can be defined as: An SAE that is considered to be a reaction to one of the supplementary therapies or a drug prescribed as part of SSMC.

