### Rationale

The results of this trial will: (a) allow people with CFS/ME, clinicians and health planners to choose treatment on the basis of both efficacy and cost; (b) provide evidence about the efficacy and adverse effects of the four treatments (APT, CBT, GET and SSMC); (c) provide the first test of SSMC plus pacing against SSMC alone; (d) indicate which patient characteristics predict a successful outcome; (e) identify which patient characteristics predict response to which treatment and (f) define the essential aspects of effective treatment as a first step toward the development of more efficient therapies.

The trial will recruit new patients from secondary care clinics run by three different disciplines (immunology, infectious disease and psychiatry) in six different centres in both England and Scotland. This recruitment plan will ensure sufficient heterogeneity to allow generalisation of the findings. We will not recruit directly from primary care because we wish to compare the efficacy of these treatments in patients whom GPs regard as requiring additional help and who are likely to have a worse prognosis (one of the recommendations CMO's report [4]). Furthermore, direct recruitment from primary care has been found to be problematic in previous studies. Two recent trials of treatment for prolonged fatigue (not CFS/ME) using large and well established primary care research networks recruited only 46 patients with CFS/ME in three years [21] and 44 patients in 2.5 years [22].

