### Trial treatments – interventions and control

There are four treatment arms. SSMC is given to all participants. Three quarters will also receive one of the following supplementary therapies: APT, CBT or GET.

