### Standardised Specialist Medical Care

*SSMC *will be given to all participants. This will include visits to the clinic doctor with general, but not specific advice, regarding activity and rest management, such as advice to avoid the extremes of exercise and rest, as well as pharmacotherapy for specific symptoms and comorbid conditions. SSMC is standardised in the SSMC Doctor's Manual. As well as this, SSMC participants, like all other participants, will already have received the Patient Clinic Leaflet (PCL). The PCL is a generic leaflet explaining what CFS/ME is, its likely causes, and available treatments. There will be no additional therapist involvement. In particular there will be no diary monitoring with consequent advice. The number of SSMC outpatient sessions will be recorded, along with any treatments given for each participant by the SSMC doctor. Participants will be seen by their SSMC doctor a minimum of three times after randomisation, with the first SSMC appointment taking place as soon as possible after randomisation, and within one month. Further sessions will be determined by clinical need. Trial therapists, participants and general practitioners can request an unplanned clinical review by the SSMC doctor.

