#### Reporting serious adverse events and reactions (SAEs and SARs)

In the event of an adverse event (AE), the centre leader or nominee will judge the seriousness of the event, the relationship to a trial supplementary therapy or SSMC prescribed treatment, clinical severity and the expectedness of the event. All SAEs must be reported by the RN to the SSMC doctor (or SSMC doctor to the RN), centre leader or nominee (e.g. another centre leader), and the trial manager immediately the RN or SSMC doctor learns of the SAE, regardless of the relationship to trial treatment. Reporting of SAEs and SARs will be carried out according to normal regulatory requirements.

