#### Data Monitoring and Ethics committee

Reports to DMEC and the main analysis itself (as far as possible) will be compiled blind to allocated treatment. DMEC reports will simply label treatments as A, B, C or D. DMEC may request unblinding only if they have serious concerns about any of the treatments. The unblinding would be handled by a third statistician independent of the TMG. The DMEC can recommend premature closure of the trial to the TSC. The circumstances for this need to be agreed by the DMEC and TSC, but we suggest the only likely scenario is if one of the trial treatments is shown to cause significant and consistent deterioration in a significant number of participants (to be quantified at the meeting of the DMEC). If one treatment arm does show consistent and reliable evidence of causing serious adverse reactions in participants, then consideration of closing that particular arm of the trial will be given. The DMEC will be asked to keep a close eye on any consistent pattern of deterioration of participants.

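### The serious adverse reaction definition covers only the drug part of SSMC, so serious reactions to SSMC's non-drug care are left out of its rate

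*Protocol article*

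**What the plan says.** The section on Serious Adverse Reactions defines a SAR as "An SAE that is considered to be a reaction to one of the supplementary therapies or a drug prescribed as part of SSMC". For the supplementary therapies the definition does not limit which aspect may cause the reaction. For SSMC it names drugs only.

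The section on Standardised Specialist Medical Care describes a wider treatment. It includes "general, but not specific advice, regarding activity and rest management", and drug treatment comes in addition to that. The section on trial treatments adds that "SSMC is given to all participants", and for one arm of four it is the whole allocated treatment.

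The section on reporting serious adverse events (SAEs) and SARs asks the centre leader or nominee to judge, among other things, "the relationship to a trial supplementary therapy or SSMC prescribed treatment, clinical severity and the expectedness of the event". This speaks of prescribed treatment where the definition speaks of a drug.

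SARs are used in three places:
- The Abstract lists adverse reactions, alongside adverse events, among the secondary outcomes.
- The Rationale says the trial will "provide evidence about the efficacy and adverse effects of the four treatments (APT, CBT, GET and SSMC").
- The Data Monitoring and Ethics committee section provides for considering closure of an arm: "If one treatment arm does show consistent and reliable evidence of causing serious adverse reactions in participants".

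**The concern.** Activity and rest advice is part of SSMC, yet a serious reaction to it has no place in the SAR category as defined. A serious reaction to the activity or rest content of APT, CBT or GET does. The article's own background (Risks and benefits; Safety of participants) identifies worsening after activity-based treatment as the disputed harm in this field, so this is a component for which like should be counted with like.

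Two things are at stake. The first is the SAR rate reported for SSMC itself, which the Rationale promises to inform. The second is consistency of classification. An assessor who follows the reporting section could judge an event related to SSMC, then find that the definition does not allow it to be called a SAR. Centres could resolve that differently.

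**Working it through.** The article gives no SAR rate, so there is no planned figure to reproduce. The check compares the wording and then works out the direction and limits of any bias.

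**Step 1: scope of each text**

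| Source | What counts on the SSMC side |
|---|---|
| Description of SSMC | Activity and rest advice, and drugs |
| SAR definition | Drugs only |
| Relatedness judgement in the reporting section | Prescribed treatment, not further defined |

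The definition is narrower than the treatment it refers to. The reporting section can be read as matching either.

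**Step 2: effect on SSMC's own SAR rate**

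Let
- d = rate of serious reactions to SSMC drugs,
- a = rate of serious reactions to SSMC advice,
- t = rate of serious reactions to a supplementary therapy.

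Assume that these rates add and that d and a are the same in every arm. In the SSMC-alone arm the current definition records d, while the full rate is d + a. The shortfall is a.

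**Step 3: effect on the difference between arms, with correct attribution**

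- Current definition: (t + d) − d = t.
- Definition that includes advice: (t + d + a) − (d + a) = t.

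The risk difference is the same, because participants in the therapy arms also receive SSMC and their reactions to its advice are excluded too. The definition differs by treatment component, not by arm.

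**Step 4: effect with misattribution**

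The Unblinding section states that research and therapy staff know the allocation. A participant in a therapy arm receives activity and rest guidance from two sources, so a reaction to the SSMC advice may be put down to the therapy. Let m be the share of advice reactions ascribed in this way, between 0 and 1.

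- Current definition: (t + d + m × a) − d = t + m × a.

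The excess is m × a. It runs from 0 (m = 0) to a (m = 1), always against the supplementary therapy. Under the wider definition, an advice reaction counts once in every arm whichever source is named, so this excess disappears.

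**Step 5: size**

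The article gives neither a nor m. As an illustration only, with 600 / 4 = 150 participants per arm and an assumed a of 1% to 4%:

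- shortfall in the SSMC-alone SAR count: 150 × 0.01 = 1.5 to 150 × 0.04 = 6 events;
- excess in a therapy arm: from 0 up to 1.5 events at 1%, and from 0 up to 6 events at 4%, depending on m.

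**Step 6: harm measures that do not depend on the definition**

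- Adverse events are defined without regard to relatedness.
- All SAEs are reported whatever their relationship to treatment, and their prevalence is to be reported at 13, 26, 39 and 52 weeks.
- The adverse outcomes (self-rated CGI of 5 to 7, or a 20-point fall in SF-36 physical function) need no attribution, and the primary analysis section plans a comparison of categorical deterioration.

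**The case against.** The strongest reply is that little depends on this. A serious reaction to SSMC advice is still an SAE, is still reported, and may also register on the CGI or SF-36. The analysis sections plan SAE prevalence and a deterioration comparison and do not name a SAR comparison. On early closure, the monitoring section calls consistent deterioration the only likely scenario, and its sentence on SARs asks for consistent and reliable evidence of causation, not a raw excess over SSMC alone. The phrase in the reporting section may simply mean prescribed drugs, in which case the two sections agree. All of this stands, and it limits the point to the SAR category.

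It does not remove the point. If the reporting section does mean drugs only, the two sections agree with each other, but both leave out part of SSMC. Reactions remain a listed outcome, and the adverse effects of SSMC remain a stated object of the trial.

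A reader might go further and infer that the definition by itself creates an excess of SARs in the therapy arms, for example 3 against 0 if 2% of each arm of 150 had a serious reaction to activity or rest advice. The documents do not support that. The therapy arms receive the same SSMC advice under the same exclusion, the 2% is an assumption, and the figure requires every advice reaction in a therapy arm to be ascribed to the therapy (m = 1). Nor can it be said that harm from SSMC advice would go unseen. It is missing from the SAR count only.

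**Conclusion.** The point holds in a limited form. As written, the SAR rate of SSMC omits non-drug reactions and is too low by the rate of serious reactions to its advice. That does not fit the aim of reporting adverse effects of all four treatments, and the wording of the definition and of the reporting section does not match.

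The SAR difference between a therapy arm and SSMC alone is unchanged under correct attribution. It is biased against the supplementary therapy only through misattribution by unblinded assessors, by an amount between 0 and the unknown advice-reaction rate. This rests on additive rates and on SSMC carrying the same advice-reaction rate in every arm. The all-cause SAE comparison and the CGI and SF-36 adverse outcomes are not affected, so the trial's safety comparison as a whole is not called into question.

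**What to change.** 1. In the Serious Adverse Reactions section, define a SAR as an SAE considered a reaction to any component of the allocated treatment: a supplementary therapy, or SSMC including its non-drug care as well as its drugs.
2. Use the same wording for the relatedness judgement in the reporting section.
3. Read SAR comparisons with SSMC alone alongside the all-cause SAE reporting and the deterioration comparison that are already planned.

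The cost is a change of wording in two places. The small downside is that SAR counts attributed to SSMC may rise slightly in all arms.

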#### Reporting serious adverse events and reactions (SAEs and SARs)

In the event of an adverse event (AE), the centre leader or nominee will judge the seriousness of the event, the relationship to a trial supplementary therapy or SSMC prescribed treatment, clinical severity and the expectedness of the event. All SAEs must be reported by the RN to the SSMC doctor (or SSMC doctor to the RN), centre leader or nominee (e.g. another centre leader), and the trial manager immediately the RN or SSMC doctor learns of the SAE, regardless of the relationship to trial treatment. Reporting of SAEs and SARs will be carried out according to normal regulatory requirements.

#### Non-serious adverse events and reactions

Non-serious adverse events or reactions will be assessed by the RN at each follow-up assessment interview. A risk assessment has been undertaken, and we have concluded that the therapies are of low risk to participants. Non-serious adverse events will be reported according to the usual regulatory requirements.

#### Follow-up after adverse events

After an SAE or SAR, a decision will be made by the centre leader as to whether the participant should be withdrawn from either their randomised treatment or from the trial, or need an alteration in their SSMC. Arrangements will be made by the centre leader for further assessment and management as required. Advice from the participant's GP, other health professionals or relevant local authorities will be sought for any instance of an SAE or SAR where further external advice is required. The RN will provide the centre leader and TM with a one month follow-up report on all SAEs and SARs. Further monthly reports should be provided in the absence of resolution. These reports will be communicated to the DMEC and MREC via the TM or trial statistician, and by the RN to the local Research and Development (R&D) office.

#### Safety of participants

There is a discrepancy between patient organisation reports of the safety of CBT and GET and the published evidence of minimal risk from RCTs. Surveys by *Action for M.E. *of its members suggest that people becoming worse with these treatments is caused by either rigidly applied programmes that are not tailored to the patient's disability, or by improperly supervised programmes [13-15]. PACE treatment manuals minimize this risk by being based on mutually agreed and flexible programmes that vary according to the patient's response. The RN will also carefully monitor for any adverse effects of the treatments.

#### Policy for deteriorating participant or one who drops out of treatment

The following policy will be enacted by the centre leader for any participant who is considered, or considers themselves, to be deteriorating, or has dropped out of treatment. The centre leader or delegated professional will undertake a detailed clinical assessment, at home if necessary, following which they will be offered appropriate help.

